#### Pilot study

The intervention processes and tools were piloted at one of the pre-implementation phase MOUs. Lessons learnt and feedback received from healthcare workers involved in the pilot study were incorporated into the final design and used to develop a referral pathway diagram (Fig. 3).

**Fig. 3 Fig3:**
[figure not shown]
Diagram of the referral pathway

### Implementation phase

The implementation phase will be used to deliver the HSS interventions selected to improve awareness, detection, referral, and treatment of CMDs and experiences of domestic violence in perinatal women attending public healthcare facilities between April and December 2021. Both clinical outcomes and implementation outcomes will be assessed.

#### Setting and participants

Three healthcare facilities will be purposively selected. Study sites will include a combination of (i) MOUs and BANC clinics situated in low-resource settings, (ii) provide care to women of mixed ancestry and Black African women, (iii) represent three of the four sub-districts within the Cape Metropolitan health district, and (iv) provide care to ≥60 pregnant women attending the facility for their first antenatal clinic appointment each month. All NPOs providing community-based support to the selected facilities will automatically be included.

The participants will include perinatal women attending the healthcare facilities, and sub-district-, facility-, and community-based healthcare workers. The following cadres of healthcare workers will be included: CBS trainers from each sub-district; PACK facility trainers based at each facility; psychiatric nurses, ANC nurses, and health promotion officers based at each facility; CHWs and OTLs employed by each NPOs supporting the selected facilities.

#### Study designs

The following study designs will be used to assess the implementation and clinical outcomes of the intervention: (i) healthcare worker survey, (ii) patient survey, (iii) observation of health promotion talks, (iv) cohort study, (v) patient file reviews, (vi) documentation review, (vii) counselling competence, and (viii) qualitative assessments. One fieldworker will be based at each of the three facilities and be responsible for all the data collection. Anticipated sample sizes are based on experience gained during the pre-implementation phase, as well as on the goal of assessing the feasibility and acceptability of the various HSS intervention components and related measures. Table 2 provides an overview of the study designs and objectives, data collection instruments, participants to be recruited, and the timing of data collection.

**Table 2 Tab2:** Implementation phase study designs, study objectives, data collection tools, study participants, and timing of data collection

Study design	Study objectives	Data collection tools	Participants	Timing of data collection
Healthcare worker survey	Assess changes in healthcare workers’ knowledge of mental illness and domestic violence and their attitudes towards people with mental health disorders and experiences of domestic violence	Self-administered questionnaires: organisational readiness for implementing change [30]; bespoke knowledge questionnaire; mental illness: Clinicians’ Attitudes Scale [31]; Professional Quality of Life Scale [32]; Effort-Reward Imbalance scale [33]	All healthcare workers involved in the intervention — CBS trainers, NPO managers, PACK facility trainers, psychiatric nurses, ANC nurses, OTLs, CHWs, health promotion officers, HIV counsellors, nursing assistants	Two timepoints — before receiving training and at the end of the implementation phase
Patient survey	Assess changes in pregnant women’s knowledge of mental illness and domestic violence and their attitudes towards people with mental health disorders and experiences of domestic violence	Self-administered bespoke questionnaire consisting of 16 questions	Pregnant women attending MOUs and BANC clinics	Two timepoints — before the delivery of health promotion talks and after delivery of the health promotion talks
Observation of health promotion talks	Assess uptake, fidelity, penetration, and sustainability of health promotion talks	Checklist to be completed by fieldworkers observing the talks		During the delivery of health promotion talks
Cohort study	Assess the presence of and risk factors for CMDs and experiences of domestic violence; assess whether the HSS interventions to improve awareness, detection, referral, and treatment resulted in improvement in clinical outcomes	Interviewer-administered questionnaires: Edinburgh postnatal depression scale [34]; psychological distress screening tool [12]; bespoke questionnaire to assess domestic violence; Household Food Insecurity and Access Scale [35]; Composite Abuse Scale [36]; WHO Disability Assessment Schedule [37]; Multidimensional Scale of Perceived Social Support [38]; Mother-to-Infant Bonding Scale [39]	Pregnant and postnatal women attending antenatal care clinics	Three timepoints — (1) when pregnant women are recruited, (2) when participants are 36 weeks pregnant, and (3) 6 weeks after participants have given birth
Patient file reviews	Assess changes in detection and referral rates of pregnant women with CMDs and experiences of domestic violence	Maternity case record [11]	Pregnant and postnatal women attending MOUs and BANC clinics	Weekly during the implementation phase
Documentation review	Assess coverage of the detection, referral, and treatment interventions	Bespoke patient registers and tracking forms	ANC nurses and OTLs	Daily during the intervention period
Counselling competence	Assess fidelity to the structured counselling format and content	Enhancing assessment of common therapeutic factors tool [40]; bespoke counselling evaluation form	Community health workers (CHWs)	During the last 2 months of the intervention
Qualitative assessments	Assess the acceptability, appropriateness, satisfaction, and feasibility of the selected HSS interventions	Topic guides for key informant interviews and focus group discussions	Pregnant and postnatal women involved in the intervention Healthcare workers involved in the intervention	During the last 3 months of the intervention

##### Healthcare worker survey

All healthcare workers involved in the implementation of a HSS intervention will be asked to complete a self-administered survey questionnaire prior to receiving training. The questionnaire will be available in participants’ home language and take 30 to 45 min to complete. In the last month of the study, healthcare workers who were actively involved in the intervention will be asked to complete the same survey questionnaire. We expect the number of healthcare workers linked to each facility to differ but estimate that between 10 and 20 healthcare workers are linked to each of the MOUs and BANC clinics. We intend to approach all healthcare workers and anticipate that at least 70% (i.e. 7–10 healthcare workers per facility) will agree to participate in the survey. The survey will be used to evaluate whether delivering the various HSS interventions resulted in a change in healthcare workers’ mental health knowledge, attitudes towards persons with mental illness, their psycho-social well-being, and their quality of life.

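### The healthcare worker survey invites all involved workers at baseline but only actively involved workers at the end, against Table 2, and its 7–10 per facility should read 7–14

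*Protocol article*

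**What the plan says.** The Healthcare worker survey section of the protocol article sets the baseline group as follows: "All healthcare workers involved in the implementation of a HSS intervention will be asked to complete a self-administered survey questionnaire prior to receiving training". For the last month of the study it says that "healthcare workers who were actively involved in the intervention will be asked to complete the same survey questionnaire". It does not say what makes involvement active.

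Table 2, under Study designs, has one participant entry for this survey, "All healthcare workers involved in the intervention", followed by a list of cadres. The timing entry in the same row is "Two timepoints — before receiving training and at the end of the implementation phase". The table makes no distinction between the two rounds.

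On purpose, the survey section states: "The survey will be used to evaluate whether delivering the various HSS interventions resulted in a change in healthcare workers’ mental health knowledge". It adds attitudes, psycho-social well-being and quality of life. Table 2 lists the Professional Quality of Life and Effort-Reward Imbalance scales among the instruments.

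On numbers, the survey section estimates that "between 10 and 20 healthcare workers are linked to each of the MOUs and BANC clinics", and anticipates that "at least 70% (i.e. 7–10 healthcare workers per facility) will agree to participate in the survey".

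**The concern.** Whether a worker is still active at the end is known only after baseline, and it may be related to what the survey measures. Workers who were trained and then did little would be in the before round and absent from the after round. Table 1 lists training of workers as an HSS intervention in its own right, so these workers received part of the programme whose effect is to be judged. The strain and reward scales may be most informative about those who stepped back.

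The choice is fixed at data collection. If inactive workers are not asked, a later analysis plan cannot recover their answers. The multiple imputation named under Data analyses would have no end-of-study observation from any inactive worker to draw on. It would have to assume, without any check, that they changed as active workers with similar baseline scores did.

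The expected sample per facility also does not follow from the two figures given beside it.

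**Working it through.** **Expected respondents.** The inputs, both from the Healthcare worker survey section, are 10 to 20 workers per facility and at least 70% participation.

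- Lower end: 0.70 × 10 = 7. This matches the stated 7.
- Upper end: 0.70 × 20 = 14. The stated figure is 10, and 10/20 = 50%.
- Could 10 arise another way? 10/0.70 = 14.3, so it would fit a facility with about 14 workers. The range 7–10 is also 70% to 100% of 10 workers, which ignores the upper bound of 20. Neither uses the stated 10–20.
- Three facilities: 3 × 7 = 21 to 3 × 14 = 42, against 3 × 10 = 30 as implied by the text. Because participation is put at 70% or more, 14 is the minimum for a 20-worker facility.

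**Effect of restricting the end survey.** Let *a* be the share of baseline workers who remain active, *d* the baseline score of active minus inactive workers, and *g1* and *g0* the gains of active and inactive workers, all in SD units. Take inactive workers' baseline as zero.

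- Change over all baseline workers: a·g1 + (1 − a)·g0.
- Unpaired estimate (active at the end minus everyone at baseline): (d + g1) − a·d. Its error is (1 − a)(d + g1 − g0).
- Paired estimate (active workers only): g1. Its error against the change in all workers is (1 − a)(g1 − g0).

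The article gives none of these inputs, so the values below are assumptions, with *a* = 0.7.

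| d | g1 | g0 | Change in all | Unpaired error | Paired error |
|---|---|---|---|---|---|
| +0.3 | 0.5 | 0.1 | 0.38 | 0.3 × 0.7 = +0.21 | 0.3 × 0.4 = +0.12 |
| +0.3 | 0.3 | 0.3 | 0.30 | 0.3 × 0.3 = +0.09 | 0 |
| −0.3 | 0.3 | 0.3 | 0.30 | 0.3 × (−0.3) = −0.09 | 0 |
| −0.3 | 0.1 | 0.3 | 0.16 | 0.3 × (−0.5) = −0.15 | 0.3 × (−0.2) = −0.06 |

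The errors scale with 1 − *a*. For the first row, the paired error is +0.20 at *a* = 0.5 and +0.04 at *a* = 0.9; the unpaired error is +0.35 and +0.07.

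If nobody changes at all (g1 = g0 = 0), the unpaired error is (1 − a)·d and the paired error is zero. With *d* = 0.5, the unpaired figure is 0.3 × 0.5 = 0.15 SD at 30% inactive and 0.5 × 0.5 = 0.25 SD at 50% inactive.

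**The case against.** A reader might infer that the design biases the change upward. The article does not establish that. The sign depends on who stays active and how their gains compare, and the table above gives errors of both signs. Upward error is plausible for knowledge and attitudes, because engaged workers may start higher or gain more. For quality of life and effort-reward imbalance, the added workload could push active workers the other way.

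A reader might also infer that a difference would appear even if no worker changed. That is true only of an unpaired comparison. Data analyses names t-tests and regression without saying paired or unpaired, and that detail may properly sit in an analysis plan that is not shown.

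It can be argued that *actively involved* is loose wording for the Table 2 population, and that change among those who delivered the programme is a fair target. Both are reasonable readings. But the two places then need to agree, and a delivery-only target needs its own definition and a matching baseline subset.

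Nor would disengagement go wholly unseen. Observation of talks, file reviews, registers, referral forms and interviews all bear on adoption and sustainability. What is lost is the knowledge, attitudes and strain of the workers who disengaged.

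On size, 0.15 SD is below the standard error of an unpaired difference with 30 workers in each round, √(2/30) = 0.26 SD. That is a fair reason for proportion in a pilot. It does not make the two groups comparable.

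On the 7–10 figure, all workers are to be approached and the only sample size calculation concerns the cohort study, so the consequence is small.

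**Conclusion.** The point holds in a limited form. The survey text and Table 2 describe different end-of-study populations, and the text selects on an undefined characteristic that arises after baseline. An unpaired result would combine change with altered composition; a paired one would speak only for workers who stayed active. With 70% active, the illustrative error relative to all baseline workers is −0.15 to +0.21 SD unpaired and −0.06 to +0.12 SD paired. These sizes rest wholly on assumed inputs, and the direction is open.

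The baseline group should be described as involved workers surveyed before training. To call it all trained workers would go beyond the text.

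The range 7–10 is an arithmetic error for 7–14. The corrected 21–42 covers facility-linked workers. Table 2 also includes community-based services trainers and NPO managers, who may fall outside that count.

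**What to change.** 1. In the Healthcare worker survey section, invite every baseline respondent still employed in the last month, whatever their level of involvement, as Table 2 implies.
2. State a definition of active involvement and record it for each worker.
3. Make within-worker change the main comparison, with active workers as a subgroup.
4. Replace 7–10 with 7–14 per facility. If a total is given, use 21–42 facility-linked workers over three facilities.

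The cost is a few more self-administered questionnaires of 30 to 45 minutes each, and one edited figure. Response will probably be lower among disengaged workers, so response should be reported by involvement.

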##### Patient survey

During the baseline data collection period (prior to delivering the HSS interventions), pregnant women awaiting their routine tests and consultations will be approached and asked to complete a self-administered survey questionnaire, available in their home language. During the implementation phase, pregnant women who received the health promotion talk will be asked to complete the same survey questionnaire immediately after the talk has been delivered. The survey questionnaire will consist of a few demographic questions; questions about their knowledge of depression, anxiety, and domestic violence; questions on attitudes towards people with mental illness and experiences of domestic violence; and questions on their health-seeking behaviour. We anticipate that 15 to 30 pregnant women will be willing to complete the survey after a talk and plan on administering the survey daily during the 2 weeks of baseline data collection and at least once per week during the implementation phase. The survey will be used to assess the effect of the health promotion talks in changing the mental health knowledge, attitudes, and health-seeking behaviour of perinatal women.

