#### Selecting the HSS interventions and implementation outcomes

Findings from the pre-implementation phase of the study were reviewed at an annual ASSET meeting [17]. The TDF [18] and the CICI framework [19] were used to identify contextual and behavioural determinants that could influence the implementation of HSS interventions and implementation outcomes that may have been missed in the ToC workshop. If there were determinants not identified in the pre-implementation phase, these were accounted for at this stage. The HSS interventions that were selected in the ToC workshop were also labelled according to the EPOC taxonomy [18, 20]. Finally, we ensured that implementation outcomes were aligned with the selected HSS interventions. Table 1 provides an overview of the contextual barriers that were identified, the HSS interventions that were selected, and the implementation outcomes that will be assessed.

**Table 1 Tab1:** Contextual barriers identified, HSS interventions selected, and implementation outcomes to be assessed during the implementation phase

Contextual barriers	HSS interventions	Implementation outcomes
Poor patient knowledge and health-seeking behaviour; high levels of stigma	**Training** — of health promotion (HP) officers to deliver health promotion talks **Health promotion** — delivery of daily health promotion talks to pregnant women	**Acceptability, appropriateness, satisfaction, and feasibility** of talks — qualitative interviews with pregnant women and HP officers **Adoption and fidelity** of talks — observation of talks and completion of a checklist **Sustainability** of daily talks — qualitative interviews with HP officers **Effectiveness** of talks — change in knowledge, attitudes, and health-seeking behaviour of pregnant women

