##### Addressing poor patient knowledge and health-seeking behaviour

Training and health promotion were selected as the HSS interventions to address poor patient knowledge of mental health and domestic violence, poor health-seeking behaviour, and the high levels of stigma among patients. The awareness raising component of the HSS programme will consist of health promotion officers or other lay healthcare workers providing daily, 5–7-min talks to groups of pregnant women in waiting areas at facilities. Information to be covered during the talks will include the signs, symptoms, risk factors and consequences of depression, anxiety, and experiences of domestic violence as well as the treatment options available.

Facility-based psychiatric nurses who were the recipients of the master training will be tasked with providing cascaded training to health promotion officers or other lay healthcare workers at facilities. Master trainers will be provided with a *Health Promotion and Awareness of Maternal Mental Health Training Manual* [25] to guide the delivery of the training content. Healthcare workers who will be trained to implement the health promotion talks will be provided with an A3 size, colour flipchart to guide the delivery of the talk.

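### The patient survey names change in health-seeking behaviour as an outcome, but a form filled in straight after a talk cannot show care-seeking caused by that talk

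*Protocol article*

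**What the plan says.** The section on addressing poor patient knowledge and health-seeking behaviour describes health promotion officers or other lay workers "providing daily, 5–7-min talks to groups of pregnant women in waiting areas at facilities". In the Patient survey section, women waiting at the clinic complete a self-administered questionnaire during a baseline period before the interventions start. During implementation, women who received a talk "complete the same survey questionnaire immediately after the talk has been delivered". The form covers demographics, knowledge and attitudes, "and questions on their health-seeking behaviour". The section closes by giving the purpose of this data collection: "assess the effect of the health promotion talks in changing the mental health knowledge, attitudes, and health-seeking behaviour of perinatal women".

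Table 1 gives the effectiveness outcome of the talks as "change in knowledge, attitudes, and health-seeking behaviour of pregnant women". Table 2 states the objective of the patient survey as "Assess changes in pregnant women’s knowledge of mental illness and domestic violence and their attitudes towards people with mental health disorders", with experiences of domestic violence added to the attitudes part; behaviour is not mentioned. Its two timepoints are "before the delivery of health promotion talks and after delivery of the health promotion talks".

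**The concern.** Health-seeking behaviour is something a woman does after she leaves the waiting room. A questionnaire completed as the talk ends comes before any opportunity for the talk to change it. The plan nevertheless names behaviour change as something this survey will assess.

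Poor health-seeking behaviour is one of the barriers the awareness component was chosen to address, and the Discussion treats better knowledge as the route to better health-seeking. If the plan is followed as written, a difference between baseline and post-talk answers on the behaviour items could be reported as an effect of the talks on behaviour. The design cannot support that conclusion.

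**Working it through.** No arithmetic applies. The point depends on when the outcome is measured, and the article calculates no sample size for this survey. The check sets the timing against what the behaviour items could mean.

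**Inputs**
- Talk: 5–7 minutes, daily, in the waiting area (section on poor patient knowledge and health-seeking behaviour).
- Post-talk form: completed at once (Patient survey).
- Comparison: a baseline survey of waiting women before the interventions begin. They are not described as the same women who are surveyed after talks.
- Later follow-up of survey respondents: none described (Patient survey; Table 2).
- Item wording and recall period for the behaviour questions: not shown. Table 2 says only that the questionnaire is bespoke and has 16 questions.
- Record of whether a respondent heard a talk at an earlier visit: none described.

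**Cases.** The items ask either what a woman has done or what she would do, and she is hearing her first talk or has heard one before.
1. *Past behaviour, first talk.* Everything she reports took place before the talk. The talk cannot have caused it.
2. *Past behaviour, earlier talk heard.* Some reported behaviour may have followed the earlier talk. With no described record of exposure, these women cannot be separated from those in case 1. Any change also coincides with nurse screening and referral, which the programme delivers in the same period.
3. *Intended behaviour, first or repeat talk.* An immediate shift is possible and can be measured, but it is a shift in intention. The outcome is then mislabelled.

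In none of these cases does the form show care-seeking caused by the talk it follows.

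**Other data sources.** The Documentation reviews section tracks take-up of referral and receipt of counselling, which is observed care-seeking. It is not linked to survey respondents or to attendance at a talk, so it does not supply the missing measure of the talks' effect. The cohort instruments listed in Table 2 include no named help-seeking measure.

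**Consistency.** The Patient survey section names three outcome domains and Table 1 names the same three. Table 2 names two of them for the survey. The domain left out is the one the timing cannot support.

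**The case against.** The best defence is that the questionnaire is not shown. Its health-seeking questions may already ask what a woman would do if distressed or abused. If so, the measurement is sound for a brief talk and only the label needs correcting. That stands: it is an inference, not a documented fact, that the items measure intention, and the fix below begins with relabelling.

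Two stronger readings are tempting, and the article does not support either.
- *That no post-talk form can capture any relevant behaviour.* Talks are daily, the survey is repeated at least weekly, and respondents are not restricted to first visits; only the cohort is. Some women could report behaviour since an earlier talk. What is missing is a way to identify them.
- *That testing knowledge and attitudes straight after the talk is a fault.* It is a legitimate measure of short-term effect. The timing is stated openly and the Patient survey section claims no retention.

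It can also be said that Table 2 is presented as an overview, and that Table 1's effectiveness line names no instrument. Both are true. The difference between the tables is therefore a mismatch to tidy, not a strong contradiction. The Patient survey section, however, assigns the behaviour outcome to this questionnaire in its own words, so the main point does not depend on either table.

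Nor can the matter be left to an analysis plan. The timing of the form is fixed here, and no analysis can recover behaviour that had no time to occur.

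**Conclusion.** The point holds for one of the survey's three named domains. As designed, the patient survey can support a statement about immediate knowledge and attitudes and, if the items ask it, intended help-seeking. It cannot support a statement that a talk changed health-seeking behaviour.

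This rests on two readings of the article: that the form does directly follow the talk, and that no delayed survey, exposure record or link to later care-seeking exists beyond what is described. If the full protocol already records earlier exposure, the attribution problem for repeat attenders shrinks, although confounding with nurse screening and referral remains.

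No size of bias can be given; the number of forms collected would not measure one. A reader might also infer that a false behaviour effect would enter the case for the later cluster trial. The article does not support that. The cluster-trial sample size draws on an effect size, an intra-cluster correlation and a baseline to follow-up correlation that are not attributed to this survey. Clinical improvement is judged on the EPDS in the cohort. What the article carries forward is lessons on feasibility, acceptability and refinement.

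**What to change.** **Restate the outcome.** In the Patient survey section and Table 1, describe the survey outcome as immediate (short-term) knowledge, attitudes and intended help-seeking, after confirming that the items ask about intention. Bring the Table 2 objective into line. This costs wording only.

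**If behaviour is to stay as an outcome:**
- Add an item asking whether, and when, the woman heard a talk at an earlier visit.
- On some of the planned survey days, give the form before that day's talk, so that women exposed earlier can report help-seeking since then.
- State in advance that the result is a programme-level association, because nurse screening and referral run alongside the talks and this comparison cannot separate them.

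This costs one item, a changed order on some days and slightly fewer immediate post-talk forms. No new visits are needed.

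A help-seeking item in the 36-week cohort interview would not solve the problem. It too would mix the talks with screening and referral, and the article describes no pre-programme comparison at that timepoint.

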#### Data analyses

A combination of mixed methods will be used to analyse the data collected. REDCap, a secure web platform for building and managing online databases and surveys, will be used to capture all quantitative data. Data will be exported to STATA/SE statistical software package version 15.1 (StataCorp., College Station, TX, USA) for analysis. Multiple imputation will be used to account for participants with incomplete data. Categorical variables will be described using frequency and percentages, and associations measured using chi-square tests. Continuous variables will be described using means and standard deviations, and associations measured using *t*-tests. Linear regression models will be used to evaluate for change in EPDS scores, adjusting for the clinic and any potential confounders. Implementation outcomes will be evaluated using multivariable regression models that adjust for relevant confounders and clinic.

Qualitative data will be analysed using NVivo 12 Pro qualitative data analysis software (QSR International Pty Ltd) [41]. Semi-structured interviews will be transcribed by bilingual speakers. Transcripts will be analysed using a thematic analysis approach to generate initial codes and define, search for, and review themes [42]. The development of initial codes will be guided to a certain degree by the interview topic guides. Further themes not captured by the initial coding will be identified through extensive reading of the transcripts and coding passages interpreted as important.

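### The patient survey attributes a before-after difference to the health promotion talks, but talk exposure coincides with the start of the whole programme, so the talks' own effect cannot be separated

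*Protocol article*

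**What the plan says.** All references are to the protocol article.

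- **Baseline group** (Patient survey): "During the baseline data collection period (prior to delivering the HSS interventions), pregnant women awaiting their routine tests and consultations will be approached".
- **Later group** (same section): once the programme is running, "pregnant women who received the health promotion talk will be asked to complete the same survey questionnaire immediately after the talk has been delivered".
- **Frequency and yield** (same section): the plan is for "administering the survey daily during the 2 weeks of baseline data collection and at least once per week during the implementation phase", and "We anticipate that 15 to 30 pregnant women will be willing to complete the survey after a talk".
- **Timing** (Table 2, Study designs): "Two timepoints — before the delivery of health promotion talks and after delivery of the health promotion talks".
- **Claim**: the Patient survey section gives the aim as "The survey will be used to assess the effect of the health promotion talks in changing the mental health knowledge, attitudes, and health-seeking behaviour of" women in the perinatal period. Table 1 lists effectiveness as an outcome of the talks, defined as a change in knowledge, attitudes and health-seeking behaviour.
- **Setting** (Setting and participants): three purposively selected facilities. No control facility is described.
- **Same phase** (Implementation phase, and the sections on detection, linkage to care and treatment): nurse screening, referral and counselling by community health workers are delivered alongside the talks.
- **Analysis** (Data analyses): "Implementation outcomes will be evaluated using multivariable regression models that adjust for relevant confounders and clinic".

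**The concern.** After the baseline weeks, no woman is surveyed before hearing that day's talk, and none is surveyed at a facility without talks. Having heard the talk and being in the programme period are the same thing in these data. The before-after difference therefore contains the talk effect plus anything else that changed when the programme began or later: a step in general awareness, a change in the mix of women attending or willing to answer, the narrowing from all waiting women to talk recipients, and, for returning women, earlier screening, referral or counselling.

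The wording gives the whole difference to one component. The healthcare worker survey and the cohort study use programme-level wording instead, speaking of the HSS interventions together. The Discussion says the findings will help refine the intervention components before a cluster randomised trial. A component-level estimate that carries programme-level change could mislead that step in either direction.

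**Working it through.** The document states no sample size, power or error rate for the patient survey, so there is no figure to reproduce. (The 225-291 per facility belongs to the cohort study and the future trial.) I made three checks.

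**1. Can the talk effect be separated?**

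| Columns in the model | Data | Rank |
|---|---|---|
| intercept, 2 clinic, talk, period | as planned | 4 of 5 |
| intercept, 2 clinic, talk, linear week | as planned | 5 of 5 |
| intercept, 2 clinic, talk, linear week, step at programme start | as planned | 5 of 6 |
| intercept, 2 clinic, talk, linear week, step at programme start | plus pre-talk forms in the implementation phase | 6 of 6 |

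A linear week term can be fitted, so steady drift can be modelled if linearity is accepted. A step at programme start cannot be separated from the talks in the planned data. Pre-talk forms collected during the implementation phase make it separable.

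**2. How large could the error be? (illustration)**

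From the document: 15-30 forms per occasion, daily for 2 weeks, at least weekly afterwards, 3 facilities. Assumed: 5 clinic days a week, 37 implementation weeks, one form per woman, outcome in SD units, talk effect zero, and a shared shift d.

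- Baseline forms: 15 × 10 × 3 = 450, to 30 × 10 × 3 = 900.
- Post-talk forms: 15 × 37 × 3 = 1,665, to 30 × 37 × 3 = 3,330.
- SE = √(1/n0 + 1/n1): √(1/450 + 1/1,665) = 0.053; √(1/900 + 1/3,330) = 0.038.
- Chance of a significant result (two-sided 5%) = Φ(d/SE − 1.96) + Φ(−d/SE − 1.96).
- With session clustering, SE is multiplied by √(1 + (m − 1) × ICC). At an assumed ICC of 0.02 the factor under the root is 1.28 for m = 15 and 1.58 for m = 30, giving SE 0.060 and 0.047.

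| Assumed shift d | Independent responses | Session ICC 0.02 |
|---|---|---|
| 0.05 SD | 16% to 27% | 13% to 19% |
| 0.10 SD | 47% to 76% | 38% to 56% |

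A second calculation used a binary item, an assumed 50% correct at baseline, 35 weeks and independent responses (450 vs 1,575, and 900 vs 3,150). A 5-point shift with no talk effect is declared a positive talk effect 47% and 76% of the time.

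**3. What does a within-session split cost in precision?**

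The detectable effect at 80% power is 2.8 × SE, without clustering.

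- Planned contrast: 2.8 × 0.0531 = 0.149 SD (15 per talk); 2.8 × 0.0376 = 0.105 SD (30 per talk).
- Within-session split, all respondents: SE = √(4/1,665) = 0.0490, giving 0.137 SD; √(4/3,330) = 0.0347, giving 0.097 SD.
- First-visit women only, at the eligibility minimum of 60 a month: 60 × 12/52/5 = 2.77 per clinic day; × 111 sessions (37 × 3) = 307 women. SE = √(4/307) = 0.114, giving 0.32 SD. At three times that volume: 0.18 SD.

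The split figures assume the scheme runs on all 37 weekly survey days. Starting mid-phase leaves fewer sessions and a larger detectable effect.

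**The case against.** The strongest reply is that this is a feasibility pilot. Table 2 speaks only of assessing changes, and Table 1 defines effectiveness as a change. An uncontrolled before-after survey is acceptable as description, so what remains is wording. Much of that stands. As description the survey needs no redesign, and rewording would remove the contradiction between claim and data. It would not tell the team what the talks themselves do, which the Patient survey section sets out to learn.

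A reader might also infer stronger points that the document does not support:

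- *No time adjustment is possible.* A linear week term can be fitted. It relies on linearity, with only 2 baseline weeks before the talks, and cannot absorb a step.
- *Screening and counselling are the main rival explanation.* The form is completed straight after a waiting-area talk, so a first-visit woman would not normally have been screened or counselled yet. Counselling is meant for women with mild to moderate symptoms. This route is open mainly for returning women, whom the survey does not exclude. Case-mix change and a programme-start step do not depend on it.
- *The false-positive rates describe this study.* They follow from assumed shifts, reflect partly that large samples detect small differences, and fall when responses cluster by session.
- *The pilot could not tell whether to keep the talks.* Table 1 also lists acceptability, appropriateness, satisfaction, feasibility, adoption, fidelity and sustainability of the talks, and no keep-or-drop rule rests on the survey.

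**Conclusion.** The concern holds as a mismatch between what the survey is said to estimate and what its data can identify. Following the plan exactly credits the talks with any step at programme start, change in case mix or, for returning women, exposure to other components. This rests on the described data collection alone and needs no assumed figure. Because it concerns who is surveyed and when, a later choice of analysis model cannot fully repair it.

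The bias equals whatever shift occurred, and the documents give no figure for that. The rates above show only that, at these sample sizes, modest shifts could pass for a talk effect. They depend on the assumed shift, clinic days, number of weeks and session correlation. The consequence is limited to the effectiveness result for the talks. A change is worth making, but the point does not undermine the pilot as a whole.

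**What to change.** **If data collection can still change** (the Methods section says the phase is in progress and enrolment is incomplete):

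1. On the remaining weekly survey days, allocate forms at random or in alternation so that about half the consenting women complete the form just before the talk and half just after.
2. Estimate the talk effect as the within-session difference among all respondents, with session as a stratum or fixed effect.
3. Record visit number, earlier talks heard and earlier screening, referral or counselling. State that the all-respondent estimate is the added effect of that day's talk, since some pre-talk women will have heard an earlier one.
4. Use first-visit women as a sensitivity analysis only. That subset is small: the detectable effect is about 0.3 SD at 60 first visits a month, assuming 5 clinic days a week and 37 weeks.
5. Keep the 2-week baseline, and report its contrast with the implementation phase as a before-after change under the whole programme.

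**If it cannot change**, reword the aim in the Patient survey section and the effectiveness entry in Table 1 to claim only that before-after change.

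**Cost.** The split uses the same fieldworker, form and number of forms. It gives about half as many post-talk forms per session, requires the fieldworker to be present before the talk, and, as a mid-study change, leaves two survey schemes to analyse and report. The rewording costs nothing.
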